## Abstract

This manuscript describes the rationale and protocol of a real-world data (RWD) study entitled Health Care and Social Survey (ESSOC, Encuesta Sanitaria y Social). The study’s objective is to determine the magnitude, characteristics, and evolution of the COVID-19 impact on overall health as well as the socioeconomic, psychosocial, behavioural, occupational, environmental, and clinical determinants of both the general and more vulnerable population. The study integrates observational data collected through a survey using a probabilistic, overlapping panel design, and data from clinical, epidemiological, demographic, and environmental registries. The data will be analysed using advanced statistical, sampling, and machine learning techniques. The study is based on several measurements obtained from three random samples of the Andalusian (Spain) population: general population aged 16 years and over, residents in disadvantaged areas, and people over the age of 55. Given the current characteristics of this pandemic and its future repercussions, this project will generate relevant information on a regular basis, commencing from the beginning of the State of Alarm. It will also establish institutional alliances of great social value, explore and apply powerful and novel methodologies, and produce large, integrated, high-quality and open-access databases. The information described here will be vital for health systems in order to design tailor-made interventions aimed at improving the health care, health, and quality of life of the populations most affected by the COVID-19 pandemic.

## 1. Introduction

### 1.1. Background

Currently underway are a large number of studies investigating the evolution of the 2019 coronavirus disease (COVID-19) and the impact it is having in terms of the number of infected patients, hospital admissions, and deaths [1,2,3,4,5,6], as well as on the mental health and well-being of the population [7]. Nevertheless, very few reports providing information concerning clinical, contextual and citizens’ general perceptions pertaining to the pandemic’s impact and evolution since its onset are being prepared [8,9,10].

The Spanish Government officially declared a State of Alarm on 14 March 2020 (Spanish Royal Decree 463/2020 [11]) in the face of the global public health emergency caused by COVID-19. Among other actions, it ordered individuals’ freedom of movement to be limited (Article 7, “Limitación de la libertad de circulación de las personas”), which was subsequently restricted even further through other decrees (hereinafter referred to as confinement). These limitations have led to a series of still little-studied problems in the population. In this sense, recent reviews of epidemic outbreaks and subsequent confinements have concluded that these actions have very negative and long-term impacts on mental health [12,13]. Likewise, this current pandemic is also seeing such negative effects, albeit in the short-term [14,15,16,17]. Furthermore, all studies agree on the urgent need for more evidence regarding the kind of impacts being experienced, in particular, evidence gathered from among the most exposed populations as well as those populations in a situation of greater vulnerability such as minors in foster care, ethnic minorities, the elderly or people with chronic diseases [8,18,19,20,21].

COVID-19impact on ethnic minorities

The results of different studies on the impact of COVID-19 on the migrant population and ethnic minorities have revealed a higher incidence of the disease in these population groups in relation to deficient conditions in terms of socioeconomic deprivation, comorbidities, unemployment, and liveability [22,23,24]. As in the case of the Roma population, this situation may be aggravated in the migrant population as they have less access to health care because of the deterioration of their socioeconomic and administrative conditions or their difficulty in understanding the prevention and health care information provided due to language limitations [25,26].

COVID-19impact on people with chronic diseases

The results of some studies into the effects of pandemics on the health of people with chronic diseases have highlighted the need to adapt health care to the confinement situation by introducing measures such as remote consultations [27,28]. Furthermore, these studies revealed that throughout the confinement period, the symptoms of some diseases, such as Alzheimer’s [29], diabetes [30] or chronic obstructive pulmonary disease (COPD) [31], were exacerbated. It is well known that health care can be affected during health emergencies and pandemics as a result of resources being diverted towards more urgent areas [32,33,34].

COVID-19impact on elderly population

In Spain, 38% of confirmed COVID-19 cases, almost half of the hospitalisations due to the virus, and more than 85% of the deaths, are among people over 70 years of age [35,36] Internationally, it has been confirmed that the elderly are at greater risk of hospitalisation and developing severe symptoms [37,38], while people over 60 and those with underlying conditions such as hypertension, diabetes, cardiovascular diseases, chronic respiratory diseases, or immunosuppression, are at greater risk of severe infection and death [39,40]. Furthermore, these extreme pandemic-related incidence and mortality rates among the elderly population are further aggravated by its psychosocial impact, with a higher risk of depressive feelings [41,42,43].

The aforementioned is a clear reflection of the tragic COVID-19 situation that is currently being experienced, and may be even harsher in deprived socioeconomic contexts [9], although these results must be further explored and there is no evidence, in this respect, in our context. Furthermore, the situation caused by the pandemic means that coordination between social and health care services, together with the provision of resources, are even more necessary and urgent than ever [44].

With respect to the health impact of COVID-19 in Spain, several studies have been launched such as the Spanish Seroepidemiology Study (Estudio Nacional de Seroepidemiología, Spain) which is based on the data obtained through a probability population-based macro-survey that provides estimates down to the provincial level, monitoring the evolution of the epidemic, and information obtained from patients’ medical records [36,45,46]. Most of the studies found are using cross-sectional designs, non-probabilistic samples, and web surveys [47,48] and represent an agile and simple alternative for collecting a large amount of data quickly and offering results practically in real-time; something which is crucial to responding to situations such as the one currently being experienced. However, they do have a number of disadvantages and limitations. For instance, they do not allow for the impact on and evolution in certain populations in more vulnerable positions to be determined, nor do they allow valid estimates to be obtained which would, in turn, allow the level of error to be limited to the appropriate standards to be conclusive. The reason for this is because they are not usually processed with a view to solving problems resulting from a lack of coverage and response, or from selection bias in the sample [49].

### 1.2. The ESSOC Study Framework

The Health Care and Social Survey (ESSOC, Encuesta Sanitaria y Social) research project arose from the need to provide data on the impact of COVID-19. Its results can then be considered when making decisions to prepare and provide an effective Public Health response in the different populations affected, especially the most vulnerable such as, among others, the elderly, the chronically ill, or those at risk of exclusion. ESSOC focuses on Public Health [50] and relies on the participation of society to obtain information on people’s health and their quality of life in order to be able to intervene both individually and collectively in the face of the pandemic (Table 1). The research project is based on a real-world data [51] design that integrates observational data extracted from multiple sources of differing natures and perspectives, i.e., both probabilistic and administrative. Thus, it will generate a very large amount of linked data from differing sources based on longitudinal probabilistic population surveys (more than 22,000 interviews with information on more than 700 variables over three years on the economic situation, state of health and well-being from the perspective of the citizens involved), and sources based on clinical (more than one million records between COVID and non-COVID cases with information on more than 110 variables over two years), epidemiological (almost 600,000 cases with information on more than 25 variables over one year), demographic (from the 8.5 million people residing in Andalusia), and environmental records (more than a million records with information on more than 20 variables over 10 years–i.e., data from an administrative perspective).

In addition, the data analyses will be performed using advanced statistical, sampling and machine learning techniques, which will allow for new research methods to be developed and implemented [52]. The research follows an Open Science approach [53] in terms of disseminating its results, methodologies, processes, and collected data, which will be distributed, reused, and freely and openly accessible to not only the scientific, academic, clinical, and public health managerial community, but also to society at large and, in particular, those population groups identified as being at greater risk of vulnerability to COVID-19. Its management model is that of collaborative and multidisciplinary research, facilitating the creation of a context of scientific cooperation in the fields of public health, health care, public administration, data science, environmental and demographic sciences, and social sciences (Table 1). Finally, the study region, Andalusia, is the most populated (8.5 million inhabitants) and the second largest in area of the 19 regions in Spain. It is also a region of interest within Europe as it is the fifth most highly-populated region. The ESSOC research project is included in the Oxford Supertracker global directory of policy trackers and surveys related to COVID-19 [1].

### 1.3. Hypotheses

Perceptions of general health, mental health, and emotional well-being could have deteriorated in the short- (one year) and mid-term (three years) since the beginning of the pandemic, with a greater impact perhaps being observed in women, young people, and those diagnosed with COVID-19.The socioeconomic, psychosocial, behavioural, occupational, environmental, and clinical determinants of health could have deteriorated since the onset of the pandemic.Health inequalities may have increased along the axes of social class, gender, age, ethnicity, and territory as a result of COVID-19, and may be even greater in the mid-term compared with the short-term.Chronicity and resulting disability may have increased significantly since the beginning of the pandemic.Since the beginning of the pandemic, the care burden has increased significantly for women in the short-term and this might have had a highly negative impact on their health and well-being.Social and emotional support in the population aged over 55 years might have decreased significantly since the beginning of the pandemic, with the greatest differences perhaps being observed in single-person households in urban areas.

### 1.4. Objectives

General: To determine the magnitude, characteristics, and evolution of the impact of COVID-19 on overall health and its socioeconomic, psychosocial, behavioural, occupational, environmental, and clinical determinants in the general population, and that with greater socioeconomic vulnerability.

Specific:To determine the short- and mid-term impact of the COVID-19 pandemic on the health and emotional well-being of the general population of Andalusia.To analyse the evolution of the socioeconomic, psychosocial, behavioural, clinical, and environmental determinants of health in the context of the COVID-19 pandemic in the population under study.To identify health inequalities along the axes of social class, gender, age, ethnicity, and territory, and their evolution in the context of the COVID-19 pandemic.To evaluate different research sampling techniques to improve the reliability and precision of estimates obtained through surveys using longitudinal designs.

## 2. Materials and Methods

### 2.1. Study Design

This study employs a real-world data design to integrate observational data extracted from multiple sources, including information obtained from different providers based on surveys and clinical, epidemiological, population, and environmental registries.

The surveys have an overlapping panel design [54] to ensure there are both cross-sectional and longitudinal estimates, and to include population-based probability samples. Thus, the ESSOC is made up of a series of measurements broken down into a new sample and a longitudinal sample for each measurement.

### 2.3. Sampling Frame

The first measurements are different for each ESSOC survey depending on the availability of the sampling frames. Therefore, ESSOCgeneral was the first survey to be carried out because the sample frame was already available, while the ESSOC + 55 sampling frame had to be developed from scratch and the ESSOCzones sampling frame had to be integrated into the same ESSOC general sampling frame to geographically identify the population located in disadvantaged zones. These areas are defined according to social (unemployment, immigration or social disintegration), urban planning (housing) and educational (illiteracy, absenteeism or school failure) criteria [55].

Thus, the sampling frame used to extract the ESSOCgeneral and ESSOCzones samples has been obtained from the Longitudinal Andalusian Population Database (BDLPA, Base Longitudinal de Datos de Población de Andalucía) [56]. The BDLPA originates from integrating data obtained from the Civil Registries with respect to births, deaths, and marriages (i.e., vital statistics (MNP, Movimiento Natural de la Población)), as well as that reported in the population and housing censuses, give rise to an integrated longitudinal frame for population and territorial statistics in Andalusia [57]. The selected samples are linked to the information obtained from the User Database (BDU, Base de Datos de Usuarios) [58] of the Andalusian Public Health Care System in order to obtain the telephone numbers of the people selected (sample units). The BDU coverage in terms of contact telephone numbers for the selected samples is usually above 96%. On the other hand, the ESSOC + 55 sampling frame corresponds to the user population of the Andalusian Guadalinfo public network aged 55 years and over [59].

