### 2.5. Sample Selection and Sample Allocation

The probability sampling method used in each measurement to obtain the ESSOC general sample is the stratified random sampling. Twenty-four strata are defined by eight provinces and three degrees of urbanisation (urban, intermediate density, and rural area) [61] (crossed stratification). Allocation of the new samples for each measurement is proportional to the population size of each stratum of province and degree of urbanisation. This implies that within each stratum (province-degree of urbanisation), any person has the same probability of being selected, that is, self-weighted samples are obtained in each stratum.

In addition, for the M5 measurement, the distribution of the new sample will be performed, in the first place, in the two DA strata and, subsequently, as in the case of the previous measurements.

The theoretical longitudinal sample of a measurement is composed of the effective sample of the previous measurement, except for measurement M1 which, being the first one, does not have a longitudinal sample.

In the ESSOC + 55 sample, the first measurement was stratified by clusters (Guadalinfo Centers, N = 651), with sub-sampling to 1200 users. These centres are stratified per Andalusian province and inhabitation level (<10,000 inhabitants, 10,000–19,999, ≥20,000), as well as sex and age quotas (55–64 years, 65–74 years, and >75 years). As in the case of the ESSOCgeneral sample, the ESSOC+55 second measurement will be made up of a longitudinal sample (that of the first measurement) and another new sample, until a total of 1200 interviews are completed.

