The limitations of the study include those derived from the coverage and quality of the sampling frames, which may cause selection biases. In the case of the BDLPA, its telephone coverage is over 90% and it tends to have low percentages of non-existent telephone numbers (7–8%) or non-contactable telephone numbers due to the frame’s outdatedness (9–10%). That said, any potential biases due to such defects will be corrected through the estimator calibration techniques described above. Another limitation is that caused by the longitudinal design of the ESSOC surveys in terms of panel attrition, which could lead to potential biases due to an absence of response. We estimate the response rate for the full longitudinal sample to be 25–35% (the effective sample in M5 of the effective sample in M1 is divided by the effective sample in M1). To reduce the effect of potential non-response biases, we decided, on the one hand, to use an overlapping panel design as this type of design allows for completing each measurement with new cross-sectional samples that become longitudinal in subsequent measurements and, on the other hand, to make adjustments in each measurement according to the weights of the longitudinal samples.

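### ESSOC+55 is described as a random sample of Andalusians over 55, but its frame holds only Guadalinfo network users, so its estimates apply to those users

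*Protocol article*

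**What the plan says.** The protocol article presents the three surveys alike. The abstract speaks of "several measurements obtained from three random samples of the Andalusian (Spain) population" and names the second and third as "residents in disadvantaged areas, and people over the age of 55". Section 2.1 says the surveys are designed "to include population-based probability samples". Section 2.2 gives the scope of ESSOC+55 as the population over 55, with no restriction to network users, and plans to compare the three populations at a common timepoint.

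The sampling sections describe something narrower. ESSOCgeneral and ESSOCzones come from the longitudinal population database (BDLPA), but section 2.3 states that "the ESSOC + 55 sampling frame corresponds to the user population of the Andalusian Guadalinfo public network aged 55 years and over". Section 2.5 describes ESSOC+55 as a stratified cluster design over 651 Guadalinfo centres, sub-sampled to 1,200 users, with strata by province and municipality size "as well as sex and age quotas (55–64 years, 65–74 years, and >75 years". Only ESSOCgeneral is called stratified random sampling there.

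The last hypothesis in section 1.3 is about the whole age group: "Social and emotional support in the population aged over 55 years might have decreased significantly since the beginning of the pandemic". The Discussion admits in general terms that sampling-frame coverage may cause selection bias, gives figures only for the BDLPA, and then says that "any potential biases due to such defects will be corrected through the estimator calibration techniques described above".

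**The concern.** A random sample of a population needs a frame in which every member has a known, non-zero chance of selection. People over 55 who do not use Guadalinfo have no chance of entering ESSOC+55, so the property claimed in the abstract and in sections 2.1 and 2.2 is not one that the design in sections 2.3 and 2.5 can deliver.

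Two uses are at stake. The first is any estimated level for all Andalusians over 55. The second is the comparison with ESSOCgeneral planned in section 2.2: a difference between the two surveys could reflect age, network membership or both, and the design cannot separate them. A reader who sees a confidence interval will take it to cover the population value, although it reflects sampling error among users only. The article itself criticises other surveys (section 1.1) for non-probabilistic samples and uncorrected coverage problems.

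**Working it through.** **The plan's own figure.** Only the ESSOCgeneral sample size is derived (section 2.4: p = 0.5, precision 2.4 points, 95% confidence, design effect 1.8, 40% non-response).

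- Effective size: 1.96² × 0.25 / 0.024² = 1,667; × 1.8 = 3,001.
- Theoretical size: 3,001 / 0.60 = 5,002.

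Both agree with the stated 3,000 and 5,000. No precision is derived for ESSOC+55.

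**Claim against design for ESSOC+55.**

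| Element | Claimed | Described |
|---|---|---|
| Population | All Andalusians over 55 (abstract, 2.2) | Guadalinfo users aged 55 and over (2.3) |
| Selection | Random, probability-based (abstract, 2.1) | Stratified clusters of centres with sex and age quotas; the draw within quota cells is not described (2.5) |
| Frame coverage | Over 90% telephone coverage, BDLPA only (Discussion) | Not given for Guadalinfo |
| Correction | Calibration (Discussion) | Margins of sex with age, province, nationality and urbanisation (2.8) |

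None of the calibration margins concerns network use. Calibration can align the age, sex and territorial make-up of the sample with the population. It cannot change the fact that everyone in each group is a user.

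**Illustrative size of the bias in a level.** The document gives neither input, so both are assumptions:

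- c = share of over-55s in the frame;
- d = difference between users and non-users that remains after calibration.

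Bias = (1 − c) × d. The 95% half-width is 1.96 × √(0.25 × 1.8 / n), with p = 0.5 assumed and the design effect of 1.8 borrowed from ESSOCgeneral:

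- n = 1,200 (section 2.5): 3.80 points;
- n = 1,350 (section 2.4): 3.58 points.

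With n = 1,200 the standard error is √(0.25 × 1.8 / 1,200) = 1.94 points. The actual coverage of a nominal 95% interval is Φ(1.96 − bias/SE) − Φ(−1.96 − bias/SE).

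| c | Bias, d = 2 | Bias, d = 5 | Bias, d = 10 | Interval coverage, d = 5 |
|---|---|---|---|---|
| 10% | 1.8 | 4.5 | 9.0 | 36% |
| 50% | 1.0 | 2.5 | 5.0 | 75% |
| 90% | 0.2 | 0.5 | 1.0 | 94% |

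**Bias in a change.** Let the user/non-user difference be d₁ at the first measurement and d₂ at the second, with c constant. The bias in the change is (1 − c) × (d₂ − d₁). It is zero when the difference is constant and appears only if users and non-users follow different trends.

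**The case against.** The frame is disclosed openly in section 2.3, and the Discussion concedes that the coverage of the sampling frames, in the plural, may bias selection. Both points are fair. But disclosing a frame does not limit the inference, and nowhere is ESSOC+55 restricted to users or their share of the age group given.

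The calibration sentence in the Discussion directly follows the figures on BDLPA telephone numbers, so it may never have been meant for Guadalinfo under-coverage. That reading is reasonable. It leaves ESSOC+55 with no stated remedy for under-coverage.

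A reader might go further in several ways that the documents do not support:

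- **That selection is non-random throughout.** Section 2.5 does not say how users were drawn within quota cells, so random selection there is neither stated nor excluded. Even if random, it is random among users only.
- **That results will look too favourable because network users are better connected.** The article does not describe what the network does or who uses it, so the direction of bias is unknown.
- **That the last hypothesis is assigned to ESSOC+55.** Section 1.3 does not say so. ESSOCgeneral also includes people over 55 and asks about social and emotional support from M2 on (Table 5).
- **That the decline in the last hypothesis must be biased.** A constant user/non-user difference cancels in a change.
- **That the municipality-size strata rule out an urban analysis.** Strata need not be analysis domains: the questionnaire in Table 5 records municipality, and section 2.9 allows urbanisation degree to be linked.

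**Conclusion.** The contradiction stands on the text alone. ESSOC+55 is labelled a random sample of Andalusians over 55, while its frame and selection support inference to Guadalinfo users aged 55 and over.

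The numerical consequence cannot be fixed from the document. With an assumed 5-point difference, the bias in a level runs from 0.5 points (90% of over-55s in the frame) to 4.5 points (10%), against a half-width of 3.6 to 3.8 points. It could therefore be negligible or larger than the sampling error, and without the frame's coverage a reader cannot tell which. These figures rest on assumed c and d, p = 0.5 and the borrowed design effect.

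The conclusion covers levels for all people over 55 and comparisons with ESSOCgeneral. It extends to changes only if users and non-users have different trends. The sampling frames of ESSOCgeneral and ESSOCzones are not affected.

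**What to change.** 1. In the abstract and section 2.2, state the ESSOC+55 target population as Guadalinfo users aged 55 and over. Stop describing it as a random or probability sample of Andalusians over 55. In section 2.5, say how users were drawn within quota cells.
2. Add to the limitations the share of Andalusians aged 55 and over who are in the Guadalinfo frame, and say that calibration does not correct for non-users.
3. Base population-level claims for the last hypothesis on ESSOCgeneral respondents over 55. That survey has a probability frame, urbanisation strata and the support items from M2 on. M2 to M4 are already collected and M5 is planned.
4. If ESSOC+55 is to be projected beyond users, benchmark it against ESSOCgeneral M3 respondents over 55, the measurement closest in time. Treat any propensity score adjustment (named in section 2.8 for non-response) as a sensitivity analysis with its covariates and assumptions stated. It depends on shared covariates explaining network use.
5. Minor: write the top quota band as 75 and over, since the printed bands leave out age 75.

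The cost is wording, one coverage figure and analyses of existing and already planned data, with no new fieldwork. The downside is a narrower claim for ESSOC+55 and probably a smaller over-55 sample for the hypothesis. If 30–40% of about 3,000 ESSOCgeneral respondents are in that age range (an assumption), that is 900 to 1,200 per measurement, against 1,200 to 1,350 in ESSOC+55.
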